## Abstract

**Background:**

Recruitment of a diverse participant pool to cancer clinical trials is an essential component of clinical research as it improves the generalizability of findings. Investigating and piloting novel recruitment strategies that take advantage of ubiquitous digital technologies has become an important component of facilitating broad recruitment and addressing inequities in clinical trial participation. Equitable and inclusive recruitment improves generalizability of clinical trial outcomes, benefiting patients, clinicians, and the research community. The increasing prevalence of online connectivity in the USA and use of the Internet as a resource for medical information provides an opportunity for digital recruitment strategies in cancer clinical trials. This study aims to measure the acceptability, preliminary estimates of efficacy, and feasibility of the Trial Library intervention, an Internet-based cancer clinical trial matching tool. This study will also examine the extent to which the Trial Library website, designed to address the linguistic and literacy needs of broader patient populations, influences patient-initiated conversations with physicians about clinical trial participation.

**Methods:**

This is a study protocol for a non-randomized, single-arm pilot study. This is a mixed methods study design that utilizes the statistical analysis of quantitative survey data and the qualitative analysis of interview data to assess the participant experience with the Trial Library intervention. This study will examine (1) acceptability as a measure of participant satisfaction with this intervention, (2) preliminary measure of efficacy as a measure of proportion of participants with documented clinical trial discussion in the electronic medical record, and (3) feasibility of the intervention as a measure of duration of clinical visit.

**Discussion:**

The principles that informed the design of the Trial Library intervention aim to be generalizable to clinical trials across many disease contexts. From the ground up, this intervention is built to be inclusive of the linguistic, literacy, and technological needs of underrepresented patient populations. This study will collect essential preliminary data prior to a multi-site randomized clinical trial of the Trial Library intervention.

**Trial registration:**

This study has received institutional approval from the Committee of Human Subjects Research at the University of California, San Francisco.

## Background

Recruitment of a diverse participant pool to cancer clinical trials is an essential component of clinical research. Improved generalizability of clinical trials benefits patients, clinicians, and the research community [1]. For patients, participation in clinical trials may render immediate and long-term benefits. Direct participation in a clinical trial leads to favorable patient experiences with the health care system [2–4]. Moreover, participants in clinical trials tend to report higher adherence to medical care plans and trust in their physicians [5]. On a broader level, diverse participant pools in cancer clinical trials are essential to ensure meaningful clinical outcomes and to avoid missing potentially viable therapeutic interventions [6–9]. Effective therapies can be overlooked, or missed entirely, in unexamined minority populations [10].

Improved representation in clinical trials by race/ethnicity, age, and sex remains a critical need [11–13]. The vast majority of publicly funded cancer phase I–III clinical trials enroll ethnically White patients younger than 65 years old [14]. Black and Hispanic patients account for less than 5% of clinical trial participants, despite comprising 12% and 16% of the US population, respectively [11, 14]. Older adults account for approximately one third of the participants in prostate, lung, breast, and colorectal cancer trials, yet account for more than one third of the patients for these major cancer types [15, 16]. The underrepresentation of women in cancer clinical trials has been found to be especially pronounced among women over 64 years of age, who are significantly less likely to enroll in clinical trials compared to men [11, 14].

In prostate cancer, clinical trial disparities based on race/ethnicity are pronounced [17, 18]. Black men are known to have an increased risk of developing and dying from prostate cancer compared to White men [19]. Despite this alarming trend, Black men are grossly underrepresented in therapeutic clinical trials [14].

Complex socioeconomic and communication barriers are major drivers of these disparities, further compounding the difficulty that already exists in clinical trial recruitment [20, 21]. More than 30% of clinical trial sites fail to recruit even a single participant, 50% of clinical trials fail to reach their enrollment goal, and fewer than 20% of clinical trials are completed on time [22, 23]. Whereas the majority of cancer patients receive their longitudinal care in community settings, the majority of clinical trials and recruitment efforts are conducted at academic medical centers and research institutions [24], imposing logistical limitations on the patient populations that can more easily be recruited.

Most recruitment efforts for cancer clinical trials utilize a variety of recruitment strategies simultaneously, including direct recruitment by physician investigator, telephone call by research coordinator, and distributed information such as print materials and websites [25, 26]. Direct recruitment through a clinician or researcher relies on identifying potentially eligible patients from their medical records or via patient databases, as well as an understanding of clinical trial availability and eligibility criteria, a process which can be resource intensive [27]. Web-based materials compose the largest proportion of distributed recruitment material (62%) and are significantly more likely to be written at higher grade level than all other printed materials [25]. The current strategies for clinical trial recruitment leave much room for improvement.

The increasing prevalence of online connectivity via home computers and mobile phones in the USA, and use of the Internet as a resource for medical information, provides an enormous opportunity for digital recruitment strategies into cancer clinical trials [23, 28]. Recent data regarding the prevalence of Internet access in the USA revealed that 81% of all US adults have a smartphone, while 73% of US adults have access to broadband Internet in their home [29]. Among medically underserved populations, such as African Americans, Hispanics, low-income adults, and those with high school education or less, the prevalence of smartphone access is above 70% for each group [29]. Among all US adults, 46% report that smartphones were their primary means of accessing the Internet [29].

Digital interventions have the potential to overcome geographical barriers, automate patient eligibility, and deliver information to a diverse patient population [30]. The vast majority of adults in the USA use the Internet as the first source of health information, even before consulting a health care provider [31]. The use of online cancer resources is also common among minorities, and Internet use among Black and Hispanic populations has increased steadily over the last 10 years [28, 32, 33]. Among older adults, we see an increasing reliance on the Internet as a resource for medical information [31, 34, 35]. Consistent with these observations, the viability of Internet-based tools as an intervention to improve clinical trial participation among more diverse patient populations has already been supported by recent studies [34, 36, 37]. Social media and targeted advertising campaigns have also become a powerful vehicle for engaging with a diverse population [36, 37].

This pilot study aims to measure the acceptability, feasibility, and preliminary estimates of efficacy of the Trial Library intervention. The preliminary efficacy of the Trial Library will be assessed by the ability of this intervention to promote discussion of clinical trials during medical oncology clinic visits and, subsequently, its ability to encourage patient enrollment in clinical trials. Trial Library is a multicomponent web-based intervention designed as an Internet resource to provide relevant clinical trial results on broadly accessible platforms, thereby providing patients with actionable information about additional medical therapies and trials that they can discuss with their physician. The Trial Library tool has been designed to be easily accessible on any computer with Internet connectivity, and a concerted effort was made during the design process to also make Trial Library easy to navigate and user-friendly on smartphones. In this way, the Trial Library intervention seeks to improve the patient navigation experience for clinical trials. This pilot study will be performed at a single site to collect essential preliminary data prior to performing a larger multi-site randomized clinical trial of the intervention among a diverse population of men with advanced prostate cancer.

## Methods/study design

### Study design

This is a non-randomized single-arm pilot study among patients with prostate cancer seen at the Helen Diller Family Comprehensive Cancer Center (HDFCCC) at the University of California, San Francisco.

### Eligibility criteria

New patients with prostate cancer presenting to HDFCCC with a life expectancy of at least 6 months, ability to read and speak English, and fill out online forms will be considered for this study. Patients already enrolled on a therapeutic clinical trial will not be eligible for this study.

### Study schema

The study schema is shown in Fig. 1. Potential participants meeting the study eligibility criteria will be identified by the study coordinator through electronic health record review 7 days prior to the clinic appointment. After check-in, all potentially eligible participants will be approached by a study coordinator, introduced to the research study, and asked to provide written informed consent on paper. The Institutional Review Board requires that all study participants be informed of the details of the study including any potential risks or benefits and that informed consent be acquired from each participant before they can be included in the study. This study requires a Health Insurance Portability and Accountability Act (HIPAA) form in order for researchers to access electronic health records and collect participant clinical and sociodemographic information. Informed consent for the survey is required for all participants; however, participants will also have the option to provide informed consent to participate in a qualitative interview. Required and optional consent for patient participation in components of this study are detailed in Table 1. Subsequent to providing informed consent, the participant will be given an iPad. Approached participants may decline to participate in the study and return the iPad to the check-in desk or the study coordinator. Physicians will be approached by a study coordinator to provide written informed consent on paper for a qualitative interview within 7 days of encounter with the study participant.

**Fig. 1 Fig1:**
[figure not shown]
Patient clinic flow on study

**Table 1 Tab1:** Required and optional consent for participation in components of Trial Library study

Components of consent	Function	Requirement for participation/inclusion
Trial Library study participation	Informs patients of the purpose and content of Trial Library, risks, and benefits of participation. Allows patients to utilize Trial Library on iPad in clinic during visit.	Yes
HIPAA form	Provides permission for researchers to access patient electronic medical record for collection of participant clinical and sociodemographic information.	Yes
Qualitative interview	Informs patient of purpose of optional follow-up qualitative interview regarding patient experience using Trial Library and potential impact of this tool on their clinic visit and their understanding and/or interest in clinical trial participation.	No

### Study intervention

The Trial Library intervention has several components summarized using TiDIER format (Additional file 1) [38]. The first component is visual, audio, and written educational content describing clinical trials. The second component is a matching tool composed of a series of visual questions, such as an image of a human body with separate selections for non-metastatic versus metastatic disease. The last component is a patient report that includes all available trial options, including the technical and plain description of clinical trial name, summary of trial description in plain English, frequency of appointments required for clinical trial, and location of trial. Participants who review the components of the Trial Library intervention will receive a printed copy of a trial matching report and return the iPad to the front desk. At the end of the clinic visit, participants will be asked to complete a post-visit survey regarding their experiences using the Trial Library intervention and interactions with their physicians. A subset of participants will be identified by convenience sampling, and all clinic physicians will be asked to participate in semi-structured interviews about their experiences with the Trial Library intervention by phone or in-person. Table 2 summarizes the interview guide questions, and their associated study themes, that will be used to conduct qualitative interviews with selected participants of this study.

**Table 2 Tab2:** Semi-structured interview guide summary and associated study themes

Question	Feasibility	Acceptability	Efficacy
Patient			
Tell me about your experience using the Trial Library website.	X	X	
What did you learn from using the Trial Library website?		X	X
How did using the Trial Library website influence your visit with your health care provider?	X		X
How did using the Trial Library website influence your interest in participating in clinical trials?			X
Physicians			
Tell me about your experience having the Trial Library pilot study take place in your clinic.	X	X	
What is the clinical value of the Trial Library resource?		X	X
How did using the Trial Library website influence your visit with your patients?	X		X

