## Discussion

This novel study leverages health information technology to develop an online informational resource for a diverse patient population. The principles that informed the design of the Trial Library intervention aim to be generalizable to clinical trials across many disease contexts. From the ground up, this resource is built to be inclusive of the linguistic, literacy, and technological needs of underrepresented patient populations.

This study will measure the acceptability of the Trial Library intervention among patients with prostate cancer seen at one academic medical center. The qualitative component of this mixed methods study will capture the participant and physician experience with the intervention. This study will provide critical preliminary data prior to a larger multi-site randomized clinical trial of the intervention. Positive results from this study would support the use of Internet-based recruitment tools as a viable method for recruiting diverse patient populations into clinical trials within a clinical setting. Additionally, preliminary data from this study may inform larger interventions delivering online health information to improve clinical trial recruitment in the community.

This study will also examine the physician perspective after incorporating a patient online trial resource in the clinical context. Given that this intervention is being tested in a closed system, the clinic, we will be able to assess the impact of the intervention on the patient and physician clinical experience. It is possible implementation of this study intervention may disrupt workflow and increase clinic length. This study is targeting new patients and measuring clinic visit time to capture these effects.

We anticipate limitations in this single site pilot study and will only capture preliminary estimates of efficacy. The intervention will only populate one clinical site’s available trials and be available in English. Future studies will include a translated copy of the website in Spanish and incorporate trial options for multiple clinical sites.

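### All five interview questions mapped to efficacy take an effect for granted, two of them a favourable one, and one physician question leaves unclear whose use of the website is meant

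*Protocol article*

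**What the plan says.** In the protocol article, the section Study intervention presents Table 2, titled "Semi-structured interview guide summary and associated study themes", and says that its questions will be used for the qualitative interviews. There are four patient questions and three physician questions, each marked for one or two of feasibility, acceptability and efficacy.

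The three patient questions marked for efficacy are "What did you learn from using the Trial Library website", "How did using the Trial Library website influence your visit with your health care provider" and "How did using the Trial Library website influence your interest in participating in clinical trials". The two physician questions marked for efficacy are "What is the clinical value of the Trial Library resource" and "How did using the Trial Library website influence your visit with your patients". The two remaining questions, one for each group, are open invitations to describe an experience and carry no efficacy mark.

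On who uses the tool, Study schema says that the participant is handed an iPad after consent. Table 1 says of the study consent: "Allows patients to utilize Trial Library on iPad in clinic during visit". Intervention development names patients and caregivers as the primary end consumers. No section describes physicians using the website.

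The Discussion names a possible harm: "It is possible implementation of this study intervention may disrupt workflow and increase clinic length".

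**The concern.** A question that assumes an effect makes it harder for the respondent to say that there was none. In Table 2 this applies to every question from which efficacy themes are to be drawn, and the two neutral questions are mapped elsewhere.

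The physician item on influence closely follows the patient item on the visit, with the other party to the visit exchanged. A physician may take it to be about their own use of the website, which the study does not provide for, or about the patients' use. If different physicians read it differently, their answers do not address the same question.

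What is at stake is the qualitative evidence, and the physician view most of all. The surveys go to patients only, so the interviews with the six physicians are the only described source of physician opinion. The results are meant to inform a multi-site randomized trial. An answer of no effect that was discouraged at interview cannot be recovered afterwards.

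**Working it through.** No sample size, power or error rate enters this point. The check is a tally of Table 2, a reading of each question, and a comparison with other sections.

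**Step 1. Tally and reading of Table 2** (F = feasibility, A = acceptability, E = efficacy)

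| Question | Marks | What it takes for granted | Direction |
|---|---|---|---|
| Patient 1, open: experience with the website | F, A | nothing | none |
| Patient 2: "What did you learn from using the Trial Library website" | A, E | something was learned | favourable |
| Patient 3: "How did using the Trial Library website influence your visit with your health care provider" | F, E | an influence | none |
| Patient 4: "How did using the Trial Library website influence your interest in participating in clinical trials" | E | an influence | none |
| Physician 1, open: experience of hosting the pilot | F, A | nothing | none |
| Physician 2: "What is the clinical value of the Trial Library resource" | A, E | clinical value exists | favourable |
| Physician 3: "How did using the Trial Library website influence your visit with your patients" | F, E | an influence | none |

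- Marks by column: F = 4, A = 4, E = 5, total 13. Marks by row: 2 + 2 + 2 + 1 + 2 + 2 + 2 = 13, so the tally is consistent.
- Efficacy-marked questions: 3 patient + 2 physician = 5 of 7.
- Efficacy-marked questions that presuppose an effect: 5 of 5. Of these, 2 presuppose a favourable one and 5 − 2 = 3 leave the direction open.
- Questions that presuppose nothing: 7 − 5 = 2, neither of them marked for efficacy.

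**Step 2. Comparison with the protocol's own wording elsewhere**

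Table 1 describes the same patient interview as covering the potential impact of the tool on the visit and on interest in trials. Electronic medical record review asks whether documented trial discussion increases, and Qualitative semi-structured interview asks whether visit time increases. Those sections leave the existence of an effect open. The five questions in Table 2 do not.

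**Step 3. The physician set**

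- Physician 1 asks about having the pilot study take place in the clinic, not about the tool itself.
- That leaves 3 − 1 = 2 physician questions on the tool. One presupposes clinical value and the other is the ambiguous item.
- The ambiguous item is also one of the two physician questions marked for feasibility (Physician 1 and Physician 3).

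**Step 4. What depends on these answers**

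- Methods says that efficacy is determined by documentation of a trial discussion in the medical record. Electronic medical record review adds recruitment at about 30 days.
- Qualitative semi-structured interview gives the purpose of the interviews as feasibility and acceptability, and calls feasibility an exploratory objective.
- The same section takes wait time and time with the provider from the real-time locating system. It compares them with 66 historical patients, using a two-sample t test for clinic time.

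No test or decision rule therefore uses the interview answers. They feed the themes only.

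**The case against.** The strongest case against runs as follows. Influence has no direction, so a longer or more confused visit, or a loss of interest in trials, answers three of the five questions directly. The other two can be answered with nothing or little. Both groups also have an open question about their experience, and the physician version is well suited to bringing out disruption of workflow. The Discussion follows its sentence on disruption by saying that visit time is measured to capture it, and the wording of a question cannot affect that measure. Table 2 is only a summary of the guide. The interviews use probes, and the full guide is not shown. In context, most physicians would take the third question to mean their patients' use.

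Much of this stands, and it rules out some stronger readings that a reader might infer:

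- That the interviews are steered towards benefit. Only two of the five questions lean that way, and the physician item on influence does not push in either direction.
- That nothing lets a respondent report a worse visit. The opening questions and the three influence questions all do.
- That the ambiguous physician item is lost to the analysis. It is unclear, and an interviewer can clarify it.
- That only patients ever use the website. This is an inference: caregivers are also named as end consumers. The document shows only that it gives the iPad to participants and describes no physician use.

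The objection does not remove the point about no effect. None of the five questions asks whether there was an effect before asking what or how. This is printed wording, not detail left to a fuller document, and unseen probes can soften it but do not correct it.

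**Conclusion.** The point holds as a minor fault of wording. All five efficacy-mapped questions presuppose an effect: two a favourable one, three one without direction. Answers of no effect are therefore discouraged. One of the three physician questions is ambiguous about whose use of the website is meant.

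The consequence is confined to the qualitative themes and falls mainly on the physician view. The primary satisfaction analysis, the record-based estimate of efficacy and the comparison of visit times are untouched. How far the themes would shift cannot be quantified from the document.

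The verdict assumes that the questions are put to respondents much as Table 2 prints them. If the full guide already has probes that ask whether the tool helped, hindered or made no difference, the effect is smaller still.

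**What to change.** Reword the five questions in Table 2 and in the interview guide so that no effect and an unfavourable effect are as easy to report as a benefit:

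- Patient 2: *What, if anything, did you learn…?*
- Patients 3 and 4: *How, if at all, did using Trial Library affect your visit (or your interest in trials), for better or worse?*
- Physician 2: *What clinical value, if any, …?*
- Physician 3: *How, if at all, did your patients' use of Trial Library affect your visits, for better or worse?*

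The two opening questions can stay as they are. The only cost is a minor amendment to the interview guide. It should be made before the interviews start, so that all respondents are asked the same questions.
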